#### **11.2.2.7 Psoriatic Assessment Impact of Disease-12**

The PsAID-12 [Gossec L. et al., 2014] will be self-administered by the participant at visits as indicated in the SOA in Section 3, Table 1.

PsAID-12 is a questionnaire including 12 health domains related to PsA. Each domain is evaluated on a scale of 0 (None) to 10 (Extreme). The 12 domains are: pain, fatigue, skin problems, work, and/or leisure activities, functional capacity, discomfort, sleep disturbance, coping, anxiety, embarrassment and/or shame, social participation, and depression.

#### **11.2.2.8 Bath Ankylosing Spondylitis Disease Activity Index**

The BASDAI [Garrett S. et al., 1994] will be self-administered by the participant at visits as indicated in the SOA in Section 3, Table 1.

The BASDAI is a validated composite index consisting of 6 participant numerical rating scales (NRS) to measure severity of the following:

- Fatigue;
- Axial involvement;
- Peripheral articular involvement;
- Localized tenderness/enthesopathy;
- Severity of morning stiffness;
- Time of morning stiffness.

Each NRS has a range of 0 to 10 where 0 represents “none” and 10 represents “very severe.” For Question 6, 0 represents no stiffness and 10 represents 2 or more hours of stiffness.

The composite BASDAI score is the mean of the 6 individual NRS scores.

### **11.2.3 Physician Assessments**

Investigators will collect clinical assessments and record data in an eCOA (Section 15.1). Calculations where required will be performed by the system.

#### **11.2.3.1 Tender Joint Count and Swollen Joint Count**

Joint counts [Duarte-García A. et al., 2019] will be performed by assessor(s) who must be well trained and part of the site personnel. Whenever possible, the same evaluator will perform these assessments at all visits.

##### Number of tender joints:

The 68 joints assessed for tenderness include the 2 temporomandibular, 2 sternoclavicular, 2 acromioclavicular joints, 2 shoulders, 2 elbows, 2 wrists, 10 metacarpophalangeal, 10 proximal interphalangeal, 8 distal interphalangeal joints of the hands, the 2 hips, 2 knees, 2 ankles, 2 mid-tarsal, 10 metatarsophalangeal, and 10 proximal interphalangeal joints of the feet.

Joints are to be scored as either tender (1) or not tender (0).

##### Number of swollen joints:

The 66 joints to be examined for swelling are the same as those examined for tenderness, however excluding both hip joints.

Joints are to be scored as either swollen (1) or not swollen (0).

Synovial fluid and/or soft tissue swelling but not bony overgrowth represent a positive result for SJC.

Data will be recorded for tender and swollen joints (right or left side), i.e., a box (no, yes, or not applicable) needs to be ticked for all joints. The total number of tender and swollen joints (right and left) will be automatically calculated.

#### **11.2.3.2 Physician's Global Assessment of Disease Activity**

PhGADA will be assessed by the investigator or a qualified designee at visits indicated in the SOA in Section 3, Table 1. PhGADA is assessed by rating the activity of PsA on the participant on a VAS of 0 (Very Well) to 100 (Very Poor).

#### **11.2.3.3 Psoriasis Area and Severity Index**

PASI [Carlin C.S. et al., 2004] will be assessed by an individual suitably qualified and experienced in the administration of this instrument, which may be the investigator or a qualified designee. This will occur at the visits indicated in the SOA in Section 3, Table 1. The PASI scores will be calculated automatically and investigators or study personnel are not to calculate it manually.

The PASI score is an established measure of clinical efficacy for PsO medications, which provides a numeric scoring for the participant's overall PsO disease state, ranging from 0 to 72. It is a linear

combination of percent of surface area of skin that is affected and the severity of erythema, infiltration, and desquamation over 4 body regions.

To calculate the PASI score, the 4 main body areas are assessed:

- Head (h);
- Trunk (t);
- Upper extremities (u);
- Lower extremities (l).

These correspond to 10%, 30%, 20%, and 40% of the total body area respectively.

The area of psoriatic involvement of these 4 areas (Ah, At, Au, and Al) is given a numerical value:

- 0 = No involvement;
- 1 = <10%;
- 2 = 10% to <30%;
- 3 = 30% to <50%;
- 4 = 50% to <70%;
- 5 = 70% to <90%;
- 6 = 90% to 100% involvement.

The signs of severity, erythema (E), infiltration (I), and desquamation (D) of lesions are assessed using a numeric scale 0 to 4 where 0 is a complete lack of cutaneous involvement and 4 is the severest possible involvement; scores are made independently for each of the areas, h, t, u, and l, and represent a composite score for each area.

An illustration of judging erythema follows:

- 0 = No erythema;
- 1 = Slight erythema;
- 2 = Moderate erythema;
- 3 = Striking erythema;
- 4 = Exceptionally striking erythema.

The PASI score is calculated according to the following formula:

$$\text{PASI} = 0.1(\text{Eh} + \text{Ih} + \text{Dh})\text{Ah} + 0.3(\text{Et} + \text{It} + \text{Dt})\text{At} + 0.2(\text{Eu} + \text{Iu} + \text{Du})\text{Au} + 0.4(\text{El} + \text{Il} + \text{Dl})\text{Al}$$

#### 11.2.3.4 Body Surface Area Affected by Psoriasis

The BSA affected by PsO will be assessed by the investigator or a qualified designee at visits indicated in the SOA in Section 3, Table 1. The palm method will be used to estimate the amount of BSA as follows:

The participant's hand, including the palm, fingers, and thumb, is used as the reference point for measuring how much of their skin is affected by PsO, representing roughly 1% of the body's surface.

- Head and neck = 10% (10 palms);
- Upper extremities = 20% (20 palms);
- Trunk = 30% (30 palms);
- Lower extremities = 40% (40 palms).

Total BSA = 100%.

#### 11.2.3.5 Leeds Dactylitis Index

LDI [Helliwell P.S. et al., 2005] will be assessed by an individual suitably qualified and experienced in the administration of this instrument, which may be the investigator or a qualified designee. This will occur at the visits indicated in the SOA in Section 3, Table 1.

The LDI basic measures the ratio of the circumference of the affected digit to the circumference of the digit on the opposite hand or foot, using a minimum difference of 10% to define a dactylitic digit. The ratio of circumference is multiplied by a tenderness score, using a modification of LDI which is a binary score (1 for tender, 0 for non-tender). If both sides are considered involved, or the circumference of the contralateral digit cannot be obtained, the number will be compared to data provided in the standard reference table for hands (Table 6) and feet (Table 7). This modification is referred to as LDI basic and will be applied in this study. The LDI requires a finger circumference gauge or a tape measure to measure digital circumference.

##### Dactylitis count

The dactylitis count is the number of fingers and toes with dactylitis, with a range of 0 to 20.

##### Presence of dactylitis

If dactylitis is present with any finger or toe, the participant is counted as a participant with dactylitis.

**Table 6 Reference Circumference for Hands (measured in cm)**

| Digit | Men | Women |
|-------|-----|-------|
| Thumb | 7.0 | 5.8   |

| Digit  | Men | Women |
|--------|-----|-------|
| Index  | 6.3 | 5.4   |
| Middle | 6.3 | 5.4   |
| Ring   | 5.9 | 5.0   |
| Little | 5.2 | 4.4   |

**Table 7 Reference Circumference for Feet (measured in cm)**

| Digit       | Men | Women |
|-------------|-----|-------|
| Central toe | 8.2 | 7.2   |
| Second      | 5.2 | 4.6   |
| Middle      | 5.0 | 4.4   |
| Fourth      | 5.0 | 4.4   |
| Little      | 5.2 | 4.5   |

#### 11.2.3.6 Enthesitis Evaluation (Leeds Enthesitis Index and Spondyloarthritis Research Consortium of Canada Enthesitis Index)

Physical examinations to assess enthesial tenderness will be carried out by the investigator or a qualified designee at the visits indicated in the SOA in Section 3, Table 1.

##### Enthesitis count

The examiner will use a standardized assessment method for each enthesal site (use of the thumb or index finger, applying enough pressure to blanch the finger about a fifth of the way from the tip of the fingernail). Tenderness on examination will be recorded as either present (1) or absent (0) for each of the sites.

The sites to be assessed are as follows:

- Greater trochanter (right/left [R/L]);
- Quadriceps tendon insertion into the patella (R/L);
- Patellar ligament insertion into the patella or tibial tuberosity (counted as one site) (R/L);
- Achilles tendon insertion (R/L);
- Plantar fascia insertion (R/L);
- Medial epicondyle (R/L);
- Lateral epicondyle (R/L);
- Supraspinatus insertion into greater tuberosity of humerus (R/L);
- Medial condyle (R/L).

The enthesitis count will be used to derive the SPARCC and Leeds Enthesitis Indices.

#### Presence of enthesitis

If enthesitis is present with any of the 6 sites used for the LEI, the participant is counted as a participant with enthesitis for the purpose of calculating enthesitis responders per the LEI.

#### Indices

LEI [Healy P.J. et al., 2008] is a validated enthesitis index that uses 6 sites for evaluation of enthesitis (lateral epicondyle humerus [R/L], Achilles tendon insertion [R/L], and medial condyle femur [R/L]), giving an overall score range of 0 to 6. The LEI demonstrated substantial to excellent agreement with other scores in the indication of PsA.

The SPARCC Index [Maksymowych W.P. et al., 2009] uses 18 sites: greater trochanter (R/L), quadriceps tendon insertion into the patella (R/L), patellar ligament insertion into the patella or tibial tuberosity (R/L), achilles tendon insertion (R/L), plantar fascia insertion (R/L), medial epicondyle (R/L), lateral epicondyle (R/L) and supraspinatus insertion into greater tuberosity of humerus (R/L). The maximum score is 16 (distal patella and tibial tuberosity considered as one site). The SPARCC Index has demonstrated consistent ability to discriminate between treatment and placebo in clinical studies of PsA.

#### **11.2.3.7 Modified Nail Psoriasis Severity Index**

The mNAPSI [Cassell S.E. et al., 2007] is a tool to assess nail involvement in participants with PsA with an index score ranging from 0 to 130 for all fingernails. The mNAPSI will be assessed by an individual suitably qualified and experienced in the administration of the instrument, which may be the investigator or a qualified designee. This will occur at the visits indicated in the SOA in Section 3, Table 1. The mNAPSI will be calculated automatically and investigators or study personnel are not to calculate it manually.

The instructions for mNAPSI are:

If you question which grade to give, your answer should be the lower of the grades. Three features or groups of features (pitting, onycholysis and oil-drop dyschromia, and crumbling) of each fingernail will be graded on a scale from 0 to 3, according to the directions below. Four features (leukonychia, splinter hemorrhages, hyperkeratosis, and red spots in the lunula) will be graded as either present or absent for each fingernail.

1. **Onycholysis:** Separation of the nail plate from the nail bed. The separated part of the nail is opaque and can have white, yellow, or greenish tinge. If there is a piece of nail missing, estimate where the nail normally would have ended at the end of the nail bed, and count that missing part as involved in onycholysis.

Oil-drop (salmon patch) dyschromia: Reddish-brown discoloration under the nail plate. Onycholysis and oil-drop dyschromia are considered together. When looking at the nail,

combine the total percentage area of the nail that is affected by either and use that combined total to score the nail ([Table 8](#)).

**Table 8 mNAPSI Scores for Onycholysis**

| Score | Percent of nail with onycholysis or oil-drop dyschromia present |
|-------|-----------------------------------------------------------------|
| 0     | No onycholysis or oil-drop dyschromia present                   |
| 1     | 1% to 10% of the nail has onycholysis or oil-drop dyschromia    |
| 2     | 11% to 30% of the nail has onycholysis or oil-drop dyschromia   |
| 3     | >30% of the nail has onycholysis or oil-drop dyschromia         |

Abbreviations: mNAPSI = modified Nail Psoriasis Severity Index

2. **Pitting:** Small, sharply defined depressions in the nail surface. Pits are discrete abnormalities (“ice-pick-like”). If there is nail plate crumbling that is confluent with pits, do not score for pits. If the pits are separate from crumbling, they may be scored regardless of whether crumbling is present or not ([Table 9](#)).

**Table 9 mNAPSI Scores for Number of Pits**

| Score | Number of Pits |
|-------|----------------|
| 0     | 0              |
| 1     | 1 to 10        |
| 2     | 11 to 49       |
| 3     | >50            |

Abbreviations: mNAPSI = modified Nail Psoriasis Severity Index

3. **Nail plate crumbling:** Crumbling or fragmentation of friable nail plate which may be associated with confluent pitting. Crumbling involves alteration of the nail plate surface. Horizontal ridging of the nail, “wave-like” appearance, and horizontal lines are all features of crumbling ([Table 10](#)).

**Table 10 mNAPSI Scores for Percent of Nail With Crumbling Present**

| Score | Number of Pits                     |
|-------|------------------------------------|
| 0     | No Crumbling                       |
| 1     | 1 to 25% of the nail is crumbling  |
| 2     | 26 to 50% of the nail is crumbling |
| 3     | >50% of the nail is crumbling      |

Abbreviations: mNAPSI = Modified Nail Psoriasis Severity Index

The next 4 abnormalities are scored only by their presence or absence. A score of 1 indicates present and a score of zero indicates not present.

1. **Leukonychia:** White spots in the nail plate due to PsO in the mid-matrix. Leukonychia are just color changes. If it appears that there is depression or irregularity to the nail surface, this may be pitting or crumbling, not leukonychia. If the leukonychia is adjacent to, or confluent with crumbling or pits, it is counted as part of the crumbling or pitting and not as a separate abnormality.
2. **Splinter hemorrhages:** Small, longitudinal, linear, dark brown hemorrhage under the fingernail.
3. **Nail bed hyperkeratosis:** Thickened keratin in the nail bed.
4. **Red spots in the lunula:** Small pink or red macules in the lunula.

### 11.3 Safety Assessments

The timing and frequency of safety assessments are described in Section 3, [Table 1](#).

#### 11.3.1 Definitions

The definition of AEs, TEAE, AESIs, and SAEs is given below. The investigator and any qualified designees are responsible for detecting, documenting, and recording events that meet the definition of an AE, AESI, or SAE and for following up AEs throughout the study and to resolution or stabilization.

##### 11.3.1.1 Adverse Events

An AE is defined as any untoward medical occurrence in a participant, or clinical investigation participant administered a pharmaceutical product, and which does not necessarily have a causal relationship with this treatment. An AE can therefore be any unfavorable and unintended sign, symptom, or disease temporally associated with the use of a medicinal (investigational) product, whether or not related to the medicinal (investigational) product.

##### 11.3.1.2 Events Meeting the Adverse Events Definition

- Any abnormal laboratory test results (hematology, clinical chemistry, or urinalysis) or other safety assessments (e.g., ECG, radiological scans, vital signs measurements), including those that worsen from baseline, considered clinically significant in the medical and scientific judgment of the investigator (i.e., not related to progression of underlying disease);
- Exacerbation of a chronic or intermittent pre-existing condition including either an increase in frequency and/or intensity of the condition;
- New conditions detected or diagnosed after the participant has signed the consent form, though it may have been present before the start of the study;
- Signs, symptoms, or the clinical sequelae of a suspected drug-drug interaction;

- Signs, symptoms, or the clinical sequelae of a suspected overdose of either study treatment or a concomitant medication. [REDACTED]

#### **11.3.1.3 Events Not Meeting the Adverse Events Definition**

- "Lack of efficacy" or "failure of expected pharmacological action" per se will not be reported as an AE or SAE. Such instances will be captured in the efficacy assessments. However, the signs, symptoms, and/or clinical sequelae resulting from lack of efficacy will be reported as an AE or SAE if they fulfill the definition of an AE or SAE;
- Any clinically significant abnormal laboratory findings or other abnormal safety assessments that are associated with the underlying disease, unless judged by the investigator to be more severe than expected for the participant's condition;
- The disease/disorder being studied or expected progression, signs, or symptoms of the disease/disorder being studied, unless more severe than expected for the participant's condition;
- Medical or surgical procedure (e.g., endoscopy, appendectomy): the condition that leads to the procedure is the AE;
- Situations in which an untoward medical occurrence did not occur (social and/or convenience admission to a hospital);
- Anticipated day-to-day fluctuations of pre-existing disease(s) or condition(s) present or detected at the start of the study that do not worsen.

#### **11.3.1.4 Serious Adverse Event**

An SAE is defined as any untoward medical occurrence that:

- Results in death. The cause of death is the AE; death is an outcome;
- Is life-threatening. The term "life-threatening" in the definition of "serious" refers to an event in which the participant was at risk of death at the time of the event. It does not refer to an event, which hypothetically might have caused death, if it were more severe;
- Requires in-patient hospitalization or prolongs existing hospitalization. In general, hospitalization signifies that the participant has been detained (usually involving at least an overnight stay) at the hospital or emergency ward for observation and/or treatment that would not have been appropriate in the physician's office or out-patient setting. Complications that occur during hospitalization are AEs. If a complication prolongs hospitalization or fulfills any other serious criteria, the event is serious. When in doubt as to whether "hospitalization"

occurred or was necessary, the AE will be considered serious. Hospitalization for elective treatment of a pre-existing condition that did not worsen from baseline is not considered an SAE;

- Results in persistent or significant disability/incapacity. The term disability means a substantial disruption of a person's ability to conduct normal life functions. This definition is not intended to include experiences of relatively minor medical significance such as uncomplicated headache, nausea, vomiting, diarrhea, influenza, and accidental trauma (e.g., sprained ankle) which may interfere with or prevent everyday life functions but do not constitute a substantial disruption;
- Is a congenital anomaly/birth defect;
- Is an important medical event. Important medical events that may not result in death, be life-threatening, or require hospitalization may be considered an SAE, when based on appropriate medical judgment, they may jeopardize the participant or the participant may require medical or surgical intervention to prevent one of the outcomes listed in this definition. Examples of such events include invasive or malignant cancers, intensive treatment in an emergency room or at home for allergic bronchospasm, blood dyscrasias, or convulsions that do not result in hospitalization, or development of drug dependency or drug abuse;
- All malignant neoplasms will be assessed as serious under "medically significant" if other seriousness criteria are not met.

On an ongoing basis, safety data (including SAEs) will be reviewed by an independent DSMB (Section 11.3.12). Details on the DSMB's members, roles, and procedures to ensure trial integrity will be available in the DSMB charter.

#### **11.3.1.5 Treatment-Emergent Adverse Event**

TEAEs are defined as any AE occurring or worsening on or after the first dose of study treatment.

[figure not shown]

#### **11.3.1.7 Extra-musculoskeletal Manifestations for Additional Monitoring**

During the monitoring of AEs and SAEs at the Week 12 Visit, EOT Visit, and Safety Follow-up Visit, the investigator is to inquire whether the participant has experienced new onset or worsening of AEs during the study that might be related to extra-musculoskeletal manifestations of PsA,

#### **11.3.1.8 Pregnancy**

Women who become pregnant during the study must be discontinued from study treatment immediately.

Pregnancy itself is not regarded as an AE unless there is a suspicion that the study treatment may have interfered with the effectiveness of a contraceptive medication. However, the outcome of all pregnancies (spontaneous miscarriage, elective termination, normal birth, or congenital abnormality) must be followed up and documented even after the participant has been withdrawn from the study.

All reports of congenital abnormalities/birth defects are SAEs. Spontaneous miscarriages, ectopic pregnancy, threatened abortion, intrauterine death, and still birth should also be reported and handled as SAEs. Elective abortions without complications should not be handled as SAEs, but should be reported as a follow-up report for the pregnancy. All outcomes of pregnancy must be reported to ICON on a Pregnancy Outcomes Report Form.

Pregnancy outcomes must be collected for the female partners of any male study participants who become pregnant within 12 weeks of their partner's last dose of study treatment. Consent to report information regarding these pregnancy outcomes should be obtained from the female partner.

Pregnancies must be reported to ICON Pharmacovigilance and Safety Services (PVSS) within 24 hours of awareness, using the reporting details provided in Section [11.3.6](#).

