| Scheduled Week                                                           | --                |        |    |    |    |    |    |                 |    |        |     |     |     |                     | 30                      |                  |
| Scheduled Day                                                            | -28 Day to -1 Day | 1      | 15 | 29 | 43 | 57 | 71 | 85              | 99 | 113    | 127 | 141 | 155 | 169                 | 8 weeks after last dose |                  |
| Visit Window (days)                                                      | --                | --     | ±2 | ±2 | ±2 | ±2 | ±2 | ±2              | ±2 | ±2     | ±2  | ±2  | ±2  | ±2                  | ±7                      |                  |
| RF, CCP antibodies                                                       | X                 |        |    |    |    |    |    |                 |    |        |     |     |     |                     |                         |                  |
| FSH testing l                                                 | X                 |        |    |    |    |    |    |                 |    |        |     |     |     |                     |                         |                  |
| Serum pregnancy testing m                                     | X                 |        |    |    |    |    |    |                 |    |        |     |     |     |                     |                         |                  |
| Urine pregnancy testing m                                     |                   | X      |    | X  |    | X  |    | X               |    | X      |     | X   |     | X                   |                         |                  |
| Urinalysis a                                                  | X                 | X      |    | X  |    |    |    | X               |    | X      |     |     |     | X                   | X                       |                  |
| Safety laboratory testing (hematology and chemistry)                     | X                 | X      |    | X  |    | X  |    | X               |    | X      |     | X   |     | X                   | X                       |                  |
| ESR                                                                      | X                 | X      |    | X  |    | X  |    | X               |    | X      |     | X   |     | X                   | X                       |                  |

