#### **8.4 End of Study Definition**

A participant is considered to have completed the study if they have completed all parts of the study, including the post-treatment safety follow-up period, which concludes with the Safety Follow-up Visit 8 weeks ( $\pm 7$  days) after the administration of the last dose of study treatment.

The end of the study is defined as the date of the last visit for the last participant in the study globally.

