- c. White blood cell count  $<3.0 \times 10^9/\text{L}$ ;
- d. Absolute neutrophil count  $<1.5 \times 10^9/\text{L}$ ;
- e. Absolute lymphocyte count  $<0.8 \times 10^9/\text{L}$ ;
- f. Platelet count  $<100 \times 10^9/\text{L}$ ;
- g. Hemoglobin  $<85 \text{ g/L}$ ;
- h. Creatinine clearance  $<60 \text{ mL/min}$  (by Cockcroft Gault formula);
- i. Any other laboratory abnormality which, in the opinion of the investigator, might compromise the participant's safety, might prevent the participant from completing the study, or might interfere with the interpretation of the study results.

*Note:* An initial laboratory result obtained at the Screening Visit may be retested one time prior to the initiation of study treatment after consultation with the medical monitor. The result of the second test will then be used.

27. Participant is enrolled in another interventional investigational device or drug study, or has been in another investigational study treatment in the last 28 days prior to the Screening Visit or within 5 half-lives of the other investigational device or study treatment prior to the Screening Visit, whichever is greater;
28. Participant is pregnant or breastfeeding, or plans to become pregnant while enrolled in the study and up to 12 weeks after the last dose of study treatment;
29. Participant has a history of chronic alcohol or drug abuse in the past year prior to the Screening Visit;
30. Participant is an employee, or direct relative of an employee, of the sponsor, at a study site, or of a third-party organization involved in the study.

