### **Highly Effective Contraception**

Women of childbearing potential must be practicing a highly effective (failure rate of <1% per year when used consistently and correctly) method of birth control, prior to receiving study treatment, during the study, and for at least 12 weeks after receiving the last dose of study treatment, consistent with local regulations regarding the use of birth control methods for participants participating in clinical studies. Highly effective methods include:

- Established use of oral, patch, injected, or implanted hormonal methods of contraception;
- Placement of an intrauterine device or intrauterine system;
- Barrier methods including a male condom plus spermicidal foam/gel/film/cream/suppository (if available in their locale) or an occlusive cap (diaphragm or cervical/vault caps) plus spermicidal foam/gel/film/cream/suppository (if available in their locale);

- Male partner sterilization (the vasectomized partner should be the sole partner for that participant);
- True abstinence (when this is in line with the preferred and usual lifestyle of the participant).

*Note:* If a female participant's childbearing potential changes after start of the study (e.g., a woman who is not heterosexually active becomes active), she must begin practicing a highly effective method of contraception, as described above.

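### The last scheduled pregnancy test for women in the trial falls 2 weeks after the last dose, although the protocol's own post-dose pregnancy precautions run 12 weeks

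*Combined protocol and SAP*

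**What the plan says.** The protocol uses 12 weeks after the last dose in three places that bear on pregnancy:

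- Appendix 2 (Section 21.2) requires women of childbearing potential to use highly effective contraception "during the study, and for at least 12 weeks after receiving the last dose of study treatment".
- Exclusion criterion 28 (Section 9.1.2) bars a participant who "plans to become pregnant while enrolled in the study and up to 12 weeks after the last dose of study treatment".
- Section 11.3.1.8 collects pregnancy outcomes for "female partners of any male study participants who become pregnant within 12 weeks of their partner's last dose of study treatment".

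For women in the trial, 11.3.1.8 states that "Women who become pregnant during the study must be discontinued from study treatment immediately". It gives no number of weeks after the last dose. It does require that pregnancies be reported to the safety unit within 24 hours of becoming known, and that every outcome be followed even once the woman has left the study. Neither duty has an end date.

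In Table 1, the row "Urine pregnancy testing" is marked at Weeks 0, 4, 8, 12, 16, 20 and 24/EOT. Its Safety Follow-up cell is empty. The urinalysis row is marked at Safety Follow-up. Table 12 (Section 11.3.7) allows extra urine hCG tests where local practice requires them, a cycle is missed or pregnancy is suspected.

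**The concern.** The duties in 11.3.1.8 start when somebody learns of a pregnancy. For most of the 12 weeks in which the protocol asks women to avoid pregnancy, no scheduled procedure would reveal one. A woman who conceives shortly after the EOT test can attend the Safety Follow-up Visit, give urine for urinalysis and leave without being tested. If she conceives after that visit, the trial depends on her reporting it unprompted.

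The adverse event system does not reliably fill the gap. Section 11.3.1.8 does not treat pregnancy itself as an adverse event unless study treatment is suspected of having interfered with a contraceptive. After the Safety Follow-up Visit, 11.3.2 asks only for serious events reasonably related to treatment.

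What is at stake is the completeness of pregnancy-outcome data on an investigational agent that, per Section 8.9, had not previously been tested in patients with psoriatic arthritis. No efficacy endpoint, estimand, power or alpha statement is affected.

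**Working it through.** This is calendar arithmetic for a participant who follows the full Part A and Part B schedule.

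**Inputs**
- Last dose of study treatment: Week 22, Day 155 (Synopsis; Table 1). Section 10 counts placebo as study treatment.
- Last active sonelokimab dose in Part B: Week 20, because the Week 22 injection is placebo in every sonelokimab arm (10.1.1). Adalimumab is active to Week 22 (10.1.3).
- Last scheduled urine pregnancy test: Week 24/EOT, Day 169 ± 2 (Table 1).
- Safety Follow-up: 8 weeks ± 7 days after the last dose (8.3.5, 8.4).
- Contraception and partner period: 12 weeks after the last dose (Appendix 2; 11.3.1.8).

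**The plan's own figures reproduce**
- Safety Follow-up = Week 22 + 8 = Week 30. Day 155 + 56 = Day 211, the nominal day in the SAP visit windows.
- Individual duration = 4 + 22 + 8 = 34 weeks, as stated.

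**From the last dose of study treatment (Week 22)**
- End of the 12 weeks: 22 + 12 = Week 34 (Day 155 + 84 = Day 239).
- Last scheduled test: 24 − 22 = 2 weeks after the dose. With ± 2 days on both visits, (169 − 2) − (155 + 2) = 10 days to (169 + 2) − (155 − 2) = 18 days.
- Weeks without a scheduled test: 12 − 2 = 10.
- Weeks after the last scheduled contact: 12 − 8 = 4, with a range from 12 − 9 = 3 to 12 − 7 = 5.

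**From the last active sonelokimab dose in Part B (Week 20)**
- End of the 12 weeks: 20 + 12 = Week 32.
- Last scheduled test: 24 − 20 = 4 weeks after the dose.
- Weeks without a scheduled test: 12 − 4 = 8.
- Weeks after the last scheduled contact: 32 − 30 = 2, with a range of 1 to 3 given the ± 1 week window.

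**Expected number of pregnancies**
The documents do not give the number of women of childbearing potential. Assume 50 to 100 of about 200 participants. Appendix 2 sets a failure rate below 1% per year for contraception used consistently and correctly. Expected count < N × 0.01 × weeks / 52.

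| Period | N = 50 | N = 100 |
|---|---|---|
| 10 weeks without a scheduled test | < 0.10 | < 0.19 |
| 4 weeks after last contact | < 0.04 | < 0.08 |

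These bounds assume consistent and correct contraceptive use throughout. Imperfect use would raise them.

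**The case against.** The strongest reply is that the reporting system for participants is already open-ended. That is correct, and it rules out two stronger readings.

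- **A shorter collection window for women than for partners.** A reader might infer this from the limit to the study period in "Women who become pregnant during the study must be discontinued from study treatment immediately". That sentence governs stopping of treatment and does not set a collection window. The only capped collection rule in 11.3.1.8 is the one for partners.
- **No reporting route after follow-up.** A reader might infer this from 11.3.2. The 24-hour rule and the outcome rule in 11.3.1.8 have no end date for participants, so a pregnancy that becomes known later is still reportable.

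Four further points have weight.

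- Testing on suspicion is allowed. A woman who conceives just after Week 24 attends the Week 30 visit about 6 weeks later, and a missed cycle would permit a test there. That depends on someone raising it, since no test is scheduled.
- The Week 22 injection is placebo in the sonelokimab arms. Measured from active sonelokimab, the gap is smaller, but it does not close.
- The footnote to the pregnancy-test rows and the consent pages are not in the text available here. Either could contain an instruction on testing or reporting after EOT.
- Nothing in the documents requires the testing schedule to match the contraception period.

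It is also tempting to extend the testing gap to US participants. The SAP gives the same visit spacing for them (last dose Week 10, EOT Week 12, follow-up 8 weeks after the last dose). Their pregnancy-test schedule is set by country-specific requirements that are not in these documents, so the extension is not supported.

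**Conclusion.** The point holds as a gap in detection. Counted from the last dose of study treatment, 10 of the 12 post-dose weeks have no scheduled pregnancy test, and the final 3 to 5 weeks have no scheduled contact. For sonelokimab in Part B, counted from the last active dose, the figures are 8 weeks and 1 to 3 weeks. Separately, 11.3.1.8 leaves the post-dose window for participants unstated while giving one for partners. Alone, that would be missing detail.

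The conclusion rests on three assumptions: the 12 weeks in Appendix 2 and exclusion 28 is the period in which the sponsor wants to know of a pregnancy (the protocol never calls it a risk period); the empty Safety Follow-up cell means what it shows; and the participant follows the planned schedule. On the assumed numbers, fewer than one pregnancy is expected in the untested weeks. This is a low-cost safety improvement and does not bear on the validity of the trial.

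**What to change.** 1. In Table 1, mark the urine pregnancy test in the Safety Follow-up column for women of childbearing potential, using the urine already collected for urinalysis.
2. At that visit, remind these women to tell the site of any pregnancy that begins up to 12 weeks after the last dose. A test at about 8 weeks cannot cover the remaining weeks, so the reminder is needed as well.
3. Reconcile 11.3.1.8 with the 12-week period in Appendix 2 by stating the post-dose window for participants explicitly, keeping the existing 24-hour reporting and outcome follow-up.

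The cost is one dipstick per woman of childbearing potential and a short protocol wording change. No visit is added, and no efficacy analysis changes.
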